The effectiveness of Tai Chi on physical and psychological well-being of college students: study protocol for a randomized controlled trial

**Objective:**

We design a strict randomized controlled trail to systematically evaluate the effectiveness of Tai Chi Chuan (TCC) exercise for physical and mental health of college students. We expect to approach the objective and effective evidence to promote the universality of TCC.

**Methods/Design**

**Study design**

The study about the effectiveness of TCC on physical health and psychosocial well-being of college students is designed as a randomized, parallel controlled, assessor and statistician single-blinded trial. The allocation of participants will be equal (1:1) to the TCC exercise group (intervention group) and the control group. All assessment will be conducted by the blinded assessors at Fujian University of Traditional Chinese Medicine Affiliated Rehabilitation Hospital, and the gymnasium of FJTCM. The TCC exercise will be conducted at the gymnasium of FuJian University of TCM, and instructed by two qualified coaches. The entire trial program is illustrated in Figure 1.

**Sample size estimation**

Sample size estimation in this RCT is based on the expected improvement of the balance ability in 12-week TCC exercise in college students. The data of our preliminary experiment showed that the means and standard deviation of the balance ability (presented by motion of ellipse area which tested by standing with eyes closed on the flat of Pro-kin system) in the college students was 531.25 and 173.78. 15% improvement of balance ability will be expected after 12 week intervention. According to the same size of the estimation formula   (set α= 0.05, β= 0.10). It is estimated that a sample size of 93 participants per group will be required, considering 10% drop-out and exit. Therefore, we will recruit approximately a total of 206 participants, 103 participants in each group.

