**Statistical analyses plan**

SPSS21.0 statistical analysis software will be used to analyze data. The primary outcomes of participants who are randomized and received at least one treatment week will be carried by the intention-to-treat (ITT) analysis. Per-protocol subjects analysis（PPS）of the primary outcomes will include participants who have completed the 24-week study without major protocol violations and have compliance rate > 85%. We will compare the results of the ITT with that PP analysis to check-up whether the results are consistent or not. The continuous variables will be expressed using means with standard deviations or medians with ranges. For the variables with a normal distribution, statistical comparisons between the groups will be made by using a *t* test. If the variables have a non-normal distribution of ordinal level, statistical comparison between groups will be made using the Mann-Whitney *U* test. Measures with a discrete distribution will be expressed as percentages and analyzed by theχ2 or Fisher’s exact test as appropriate. A general linear model or Logistic regression model will be applied to adjust the confounding influence if necessary. The *p* value is less than or equal to 0.05 will be considered as a test by the difference has statistical significance.

Participants’ recruitment

Eligible patients n=206

Baseline assessment

Exclusion (reasons): n=

Not meeting inclusion criteria: n=

Declined to participate: n=

Other reasons: n=

Randomization allocation

TCC training group

n=103

Control group

n=103

Drop out (reasons): n=

TCC training group: n=

Control group: n=

Outcome assessment after intervention: balance ability, lower limbs proprioception, flexibility, physical fitness, self-efficiency, psychological symptoms ,attention, stress, self-esteem, mood and mindfulness, quality of life, quality of sleep, safety outcomes.

Follow up for 12 weeks

Lost to follow up: n=

TCC training group: n=

Control group: n=

Outcome assessment after follow-up period

Included analysis: n=

TCC training group: n=

Control group: n=

Statistic analysis

Excluded from analysis: n=

TCC training group: n=

Control group: n=

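### The stated 93 and 103 per group do not both follow from the protocol's inputs with one 10% drop-out allowance; on a two-sided test the plan gives about 87% power, not 90%

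*Protocol*

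**What the plan says.** The protocol's Sample size estimation section rests on one measure, the eyes-closed ellipse area on the Pro-kin system. The preliminary mean and SD are given as "in the college students was 531.25 and 173.78", and the target is stated as "15% improvement of balance ability will be expected after 12 week intervention". The error rates are "set α= 0.05, β= 0.10". The result is "It is estimated that a sample size of 93 participants per group will be required, considering 10% drop-out and exit", followed by "Therefore, we will recruit approximately a total of 206 participants, 103 participants in each group".

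Study design sets 1:1 allocation. Participants and Recruitment repeats the total of 206, and the flow diagram repeats 103 per group. The Statistical analyses plan section names a between-group t test for normally distributed variables, with the threshold "value is less than or equal to 0.05 will be considered as a test by the difference has statistical significance". No section says whether tests are one-sided or two-sided. The sample size formula itself does not appear in the text available for this review.

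**The concern.** Two things catch the eye. First, a standard two-sample calculation from the stated inputs gives 100 per group, not 93. Second, the sentence that gives 93 says drop-out has already been considered, yet the next sentence raises the number by about another 10% to reach 103. A reader cannot tell whether 93 is the number before or after loss.

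This paragraph is the only justification for enrolling 206 students. If the test is two-sided, the 90% power claimed is not what the plan gives after its own expected loss. If the test is one-sided, the derivation counts drop-out twice. Either way the chain from inputs to enrolment needs correcting.

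**Working it through.** **Inputs (Sample size estimation, Study design)**
- Mean 531.25, SD 173.78, improvement 15%, α = 0.05, β = 0.10, drop-out 10%, allocation 1:1.
- Assumption: the 15% is the difference between groups, with no change in controls. Δ = 0.15 × 531.25 = 79.69.
- Standardised difference d = 79.69 / 173.78 = 0.4586, so d² = 0.2103.

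**Trying to reproduce 93**

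Formula per group: n = 2(z_α + z_β)² / d², with z_β = 1.2816.

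| Test | Completers, normal formula | Completers, t test | Recruited, n/0.9 (normal; t) |
|---|---|---|---|
| Two-sided, z_α = 1.96 | 2 × 10.508 / 0.2103 = 99.9, so 100 | 100.9, so 101 | 112; 113 |
| One-sided, z_α = 1.6449 | 2 × 8.564 / 0.2103 = 81.5, so 82 | 82.1, so 83 | 92; 93 |

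- As a number of completers, 93 matches neither row.
- As a number that already includes 10% loss, 93 matches the one-sided t calculation: 83 / 0.9 = 92.2, rounded up to 93.

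**The step from 93 to 103**
- 93 / 0.9 = 103.3 and 93 × 1.1 = 102.3, so 103 is 93 with a 10% allowance added.
- If 93 is before loss, the 10% is applied once, but 93 does not follow from the inputs.
- If 93 is after loss, it can follow from a one-sided t test, but 103 then applies the 10% a second time.
- None of the usual variants tried (one- or two-sided, normal or t, dividing by 0.9 or multiplying by 1.1) gives both 93 and 103 with one allowance.

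**Power of the plan as written**

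103 × 0.9 = 92.7, so 92 to 93 completers per group. For Δ = 79.69 by t test:

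| Analysed per group | Two-sided | One-sided |
|---|---|---|
| 92 | 87.2% | 92.7% |
| 93 | 87.5% | 92.9% |
| 100 | 89.7% | 94.4% |
| 101 | 90.0% | 94.6% |
| 103 (no loss) | 90.6% | 94.9% |

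With 93 per group, a two-sided t test has 90% power only for a difference of 83.0 units, and 83.0 / 531.25 = 15.6%.

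**Baseline adjustment**

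Adjusting for baseline multiplies the SD by √(1 − r²), where r is the baseline-outcome correlation. With 92 per group and r = 0.30, two-sided power is 90.0%, with no margin.

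**The case against.** The strongest reply is that the shortfall depends on a two-sided test, which the protocol does not state. If the test is one-sided, power with 92 to 93 completers is about 93% and β = 0.10 is met. With the formula unavailable, this reading cannot be ruled out. It also matches the literal wording, in which 93 already considers drop-out. This stands, and it limits the conclusion. It does not rescue the paragraph, because 103 would then contain a second drop-out allowance. Nothing in the protocol declares a one-sided test; the Statistical analyses plan section speaks of a difference between groups without direction, for which two-sided is the ordinary reading.

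A second reply is that the effect is small. Under the two-sided reading the loss is under 3 percentage points, and none remains if all 103 per group contribute data. The intention-to-treat set covers everyone randomised with at least one treatment week, so the full number is possible in principle. That is also fair, but the protocol's own 10% allowance assumes otherwise.

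A reader might go further and infer that, if 93 already includes drop-out, only about 84 per group (93 × 0.9 = 83.7) would complete and power would fall to 84%. The documents do not support this. Recruitment is fixed at 103 per group however 93 was derived, so 10% loss leaves 92 to 93 in every case. That 103 × 0.9 = 92.7 falls just under 93 is only rounding.

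**Conclusion.** The point holds in a limited form. The figures 93 and 103 do not both follow from the stated inputs with one 10% allowance, and this does not depend on sidedness.

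If the test is two-sided and the 15% is the between-group difference, 90% power needs 100 completers per group (101 by t), or about 112 recruited and 224 in total, against 103 and 206 planned. After 10% loss the plan has about 87% power (87.2% to 87.5%), some 2.5 to 3 points below the claim. If the test is one-sided, power exceeds 90% and the error is a double allowance.

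A flat statement that β = 0.10 is not delivered would go too far, because it turns on a sidedness that the protocol leaves open. The shortfall is modest and does not undermine the trial. It is a correction that should be made to a figure on which the enrolment rests.

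**What to change.** Keep 206 participants and reword the one paragraph in Sample size estimation:

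- State that the test is two-sided, once the sponsor has confirmed it.
- State that 103 per group are recruited and that 92 to 93 are expected to remain after 10% loss.
- Replace β = 0.10 with about 87% power for a 79.7-unit (15%) between-group difference by t test at α = 0.05.
- If a one-sided test was in fact used, say so and take the second drop-out allowance out of the derivation.

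A claim of at least 90% power through baseline-adjusted ANCOVA should be made only if data support a baseline-outcome correlation of at least about 0.3. The protocol reports a single preliminary mean and SD and no correlation, so the sponsor would have to supply it.

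The cost is a slightly less favourable stated power. No extra participants are needed.

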**Participants and Recruitment**

A total of 206 participants will be recruited at FJTCM. We plan to well-advertised the recruitment program through advertisements in the campus bulletin board and the campus radio. The interested students will contact the research assistants and will be screened according to the inclusion and exclusion criteria. The potential participant will be required to sign the informed consent if they fulfill inclusion criteria and do not have any exclusion criteria before enroll in this trial.

**Inclusion criteria**

Participants have to fulfill the following criteria:

①Age from 16 to 25 years.

②A full time freshman or [sophomore](app:ds:sophomore).

③Written informed consent for participation in the trial.

**Exclusion criteria**

Students would be ineligible if they meet any condition as following:

①A long-term exercising TCC or other Tai Chi derived movements

②A member of Students' Wushu Association or Taekwondo Association or Aerobic Association or Dance Association.

③Severe cardiovascular disease or Musculoskeletal Disease

**Withdrawal criteria** Participants will be withdrawn from the trial if they present following conditions:

①Poor compliance (mean compliance < 85% at the last estimation) or noncompliance.

②Occurrence of a serious adverse event.

③Initiative exit.

④Unable to progress because of sudden disease.

⑤Members in the control group have been regularly engaged in the TCC exercise.

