**Intervention**

**TCC training group**

Participants allocated to the TCC training groups will receive 12 weeks of TCC training. The TCC training will be instructed by two experienced TCC coaches, who have been qualified and engaged in the teaching of TCC course for at least 15 years. The 24 forms simplified TCC, which is recommended as the popularity health sport by General Administration of Sport of China, will be applied to members of the intervention group. Participants of TCC training group will be gathered to exercise at the campus gymnasium together. TCC training will be performed for 60 minutes per time and also include 10 minutes of warm-up (e.g., weight shifting, arm swinging, gentle stretches of the neck) at a frequency of five days a week. Participants will be taught the “meditation through movement” art of TCC, which includes the rationale states of TCC constitute, action essence of TCC, the TCM philosophy opinion of TCC, and deep breathing method. The instruction of TCC will be both verbal and visual. The systematic approach has been designed by two coaches and can be viewed on DVD.

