**Safety** **evaluation**

Any adverse events (defined as any functional lesion caused by the intervention, such as knee joint or ankle sprain, knee soreness, lumbar muscle strain and so on) will be recorded on case report form (CRF) during intervention period. If any adverse event occurs, the coaches or project managers will provide the corresponding treatment to the participant. The adverse events will be immediately reported to the primary investigator and ethics committee to decide if the participant needs to withdraw the trial.

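### The withdrawal criteria take randomised students out of the trial, not only out of TCC, and provide for no later assessment, which undermines the planned ITT analysis

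*Protocol*

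**What the plan says.** Under Withdrawal criteria (protocol, following Exclusion criteria), a five-item list is introduced by "Participants will be withdrawn from the trial if they present following conditions". The items are: (1) mean compliance below 85% at the last estimation, or noncompliance; (2) a serious adverse event; (3) the participant's own exit; (4) sudden disease; (5) a control regularly doing TCC. The rule concerns the trial, not the training. Compliance is not defined, and no section describes assessments after withdrawal.

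The Statistical analyses plan section states: "The primary outcomes of participants who are randomized and received at least one treatment week will be carried by the intention-to-treat (ITT) analysis". It also plans a per-protocol set of students who finish the 24-week study "without major protocol violations and have compliance rate > 85" per cent, and a check of whether the two analyses agree.

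Under Safety evaluation, adverse events are "reported to the primary investigator and ethics committee to decide if the participant needs to withdraw the trial".

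Figure 1 places a drop-out box ahead of the post-intervention outcome assessment and ends with a box for exclusions from analysis. Table 1 schedules the outcome assessments at weeks 13 and 25. The stated objective is to "systematically evaluate the effectiveness of Tai Chi Chuan (TCC) exercise for physical and mental health of college students".

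**The concern.** Items 1, 2, 4 and 5 all arise after randomisation, and each is tied to adherence, harm or crossover. If such students leave the trial itself, the ITT analysis is meant to include them but has no later outcomes for them. The rules also differ partly by arm. Item 5 can apply only to controls. Item 1 falls mainly on the TCC arm if compliance means attendance, because controls are given no exercise programme.

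What is at stake is the randomised comparison on which an effectiveness claim rests. A statistical analysis plan, if one exists, cannot repair this. It can define sets and imputation rules, but it cannot recover outcomes that were never collected, and imputation here would rest on untestable assumptions about why students left.

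**Working it through.** **1. The plan's own figures.** For balance (ellipse area), Sample size estimation gives a mean and SD "in the college students was 531.25 and 173.78", and says "15% improvement of balance ability will be expected after 12 week intervention".
- Planned effect: 0.15 × 531.25 = 79.69 units, and 79.69 / 173.78 = 0.459 SD.
- Sample size with α = 0.05 and 90% power: 2 × (z for α + z for power)² / 0.459² gives 82 per group one-sided (83 with the t distribution) and 100 two-sided (101 with t).
- 83 / 0.9 = 92.2, rounded up to 93. So the stated 93 is reproduced only as a one-sided figure with drop-out already included. Then 93 × 1.1 = 102.3, rounded up to 103.
- The present point does not depend on that ambiguity. It uses only 103 per arm, the SD and the planned effect.

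**2. What 85% would mean if compliance is attendance (assumed).** Sessions are held "at a frequency of five days a week" for 12 weeks: 5 × 12 = 60. Then 0.85 × 60 = 51, so missing more than 9 sessions puts a student below the limit. Attending four of five sessions each week gives 48/60 = 80%, also below it.

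**3. Withdrawal rule against analysis sets.** Withdrawal applies below 85%, and the per-protocol set requires more than 85%. On compliance, only a student at exactly 85% falls between the two. Once the others have been withdrawn, later ITT data approach the per-protocol data.

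**4. Withdrawal rule against the safety section.** Item 2 makes withdrawal follow from a serious adverse event. Safety evaluation leaves withdrawal after an adverse event to a decision by the primary investigator and ethics committee. The two passages conflict.

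**5. Power (secondary).** Normal approximation, two-sided 5%, effect 79.69. With all 103 per arm followed, power is 90.8%. If a share of the TCC arm only is lost, it is 89.3% (10%), 87.3% (20%) or 84.8% (30%). If the same share is lost in both arms, it is 87.7%, 83.7% or 78.6%.

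**6. Bias.** The documents give neither the share w of the TCC arm withdrawn without outcomes nor the prognostic difference k (in SD) between withdrawn and retained students, so both are assumed. The control arm is taken as complete and TCC as having no effect.
- Shift b = w × k × 173.78.
- SE = 173.78 × √(1/(103(1 − w)) + 1/103).
- Two-sided type I error = P(Z > 1.96 − b/SE) + P(Z < −1.96 − b/SE).

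For w = 0.2 and k = 0.5: b = 17.4, SE = 25.7 and b/SE = 0.68, so the error is P(Z > 1.28) + P(Z < −2.64) = about 10.4%.

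| w | k | Shift (units) | Share of 79.69 | Type I error |
|---|---|---|---|---|
| 0.1 | 0.25 | 4.3 | 5% | 5.3% |
| 0.1 | 0.5 | 8.7 | 11% | 6.4% |
| 0.2 | 0.25 | 8.7 | 11% | 6.3% |
| 0.2 | 0.5 | 17.4 | 22% | 10.4% |
| 0.3 | 0.25 | 13.0 | 16% | 7.8% |
| 0.3 | 0.5 | 26.1 | 33% | 16.4% |

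The sign of k is unknown. Reversing it reverses the shift and leaves the two-sided error unchanged.

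**The case against.** The best defence is that the protocol never says assessments stop at withdrawal. It plans an ITT analysis and a contrasting per-protocol set, which makes most sense if lower compliers do have outcomes. This stands as far as it goes: loss of outcomes is an inference. It is still the natural reading of leaving the trial, it fits the position of the drop-out box in Figure 1, and nothing in the text provides otherwise.

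Second, item 1 refers to the last estimation. A reader might infer a running rule under which a student is out on missing the tenth session. The text does not establish that. Compliance may be judged at or near the end of training, when week-13 data could still be obtained. Week 25 would remain at risk.

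Third, compliance may not mean attendance. All participants keep activity diaries (Intervention regimen), so item 1 could reach controls too. The 51-of-60 figure is therefore conditional.

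Fourth, the size is assumed. A 20% loss is double the protocol's 10% drop-out allowance, and a 0.5 SD difference exceeds the whole planned effect of 0.459 SD. At 10% loss the error is only about 5.3% to 6.4%. This objection stands and limits what can be said about magnitude, but it does not remove the defect.

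**Conclusion.** The point holds as a conflict within the protocol. The withdrawal rule, followed as written, undermines the stated ITT analysis through loss related to adherence, harm and crossover, under rules that differ partly by arm. It also leaves the planned ITT versus per-protocol comparison with little to reveal.

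Three stronger conclusions might be inferred, and the documents do not support them:
- That the trial cannot measure effectiveness as randomised. An ITT analysis is planned, and data collected before withdrawal can enter it.
- That the ITT and per-protocol results must agree. A student who leaves after week 13 has week-13 data for ITT but is outside the per-protocol set, so the sets tend to converge without being identical.
- That the bias favours TCC. Nothing in the protocol shows that withdrawn students have worse balance, so the direction is unknown.

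On the assumed ranges in the working, the shift is 4 to 26 units (5-33% of the planned effect) and two-sided type I error is about 5.3% to 16.4%. The lower part of that range applies if losses stay at the protocol's 10%. The power loss is modest by comparison when only the TCC arm is depleted.

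**What to change.** Amend Withdrawal criteria to separate stopping TCC from leaving the study:
- State that items 1, 2, 4 and 5 do not by themselves end outcome collection. These students are invited to the scheduled week-13 and week-25 assessments and analysed in the group to which they were allocated.
- Record non-compliance, or TCC uptake by a control, as a protocol deviation used only to define the per-protocol set, and define how compliance is measured and when.
- Keep the participant's own exit (item 3) as a reason to end data collection, consistent with the right to withdraw under Ethical consideration.
- Reconcile item 2 with Safety evaluation on who decides about withdrawal after a serious adverse event. Whether training continues after an event is for the protocol's safety process and is not prescribed here.
- Adjust Figure 1 so that stopping the training and leaving the study are counted separately.

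The cost is a wording amendment and a few more attendances at visits already planned. Including low compliers may make the estimated effect somewhat smaller.

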**Ethical consideration**

This study protocol adheres to the principles of the Declaration of Helsinki and has been approved by the ethics committee of FJTCM (No. 042). The written consent will be obtained form each participants before the baseline assessment. All participants will have the right to withdraw from the study at any time.

**Randomization and allocation concealment**

Participants will be randomly allocated to the TCC training group or the control group. Randomization will be performed at post-baseline assessment. The randomization list will be generated via Statistical Analysis System (SAS, version 9.1) by an independent non-investigator who works in Center for EBM of Academy of Integrative Medicine FuJian China. The allocation sequence will be concealed through a password access files which will be taken care of by the project manager. The eligible participants will be informed the allocated result by the project manager after post-baseline assessment.

